### Sample size calculation

2.5

Our study is the first sham-controlled acupuncture trial that uses the Food and Drug Administration (FDA) recommended end point for IBS-C. The sample size was determined based on the study’s objectives, statistical precision, feasibility, and previously reported clinical response rates in IBS-C acupuncture trials. We referenced a randomized controlled trial by Pei et al. (28), which reported a significant difference in clinical effective rates between the acupuncture and control group. Assuming a two-sided alpha of 0.05, power of 80%, an expected response rate of approximately 70% in the acupuncture group versus 30% in the sham control group, and accounting for a 20% dropout rate and potential missing data, a total sample size of 60 patients (30 in the experimental arm and 30 in the control arm) was designed to detect clinically meaningful differences.

### Randomization, blinding and concealment

2.6

Simple, complete, non-sequential random numbers were generated in advance by a computer program in blocks of four by a statistician from a third-party institution and were kept by the principal investigator. After a participant’s eligibility is confirmed, a randomization number which corresponds to the group allocation is provided to the acupuncturist. This arrangement ensures that both the clinical assessor and participants are blinded to the allocation. To strengthen the blinding effect, eye masks are used to cover the participants’ eyes during the treatment.

The trial uses patient-blind technique, which means needles for EA and sham acupuncture are of identical looking and use same package. The study remains blinded until the final statistical analysis and the preparation of the final report. In the event that emergency code-breaking is required, the principal investigator will be informed. Investigators who break the code must document the reasons in the patients’ notes. Emergency code-breaking may occur under specific circumstances, including but not limited to (1): a serious adverse event (SAE) that is considered to be related to the interventions; or (2) a serious complication arises.

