### Outcomes and data collection

2.4

Daily symptoms recorded in physical or online patient diary include the number of BMs, SBMs, CSBMs, along with the severity of abdominal pain, discomfort, straining, and bloating, assessed using an 11-point scale (0 = none, 10 = worst possible). For each BM, stool consistency (7-point Bristol Stool Form Scale), sensation of severe straining during defecation, and use of medication are also recorded. Data will be entered electronically and stored in an encoded database within 24 h of receipt, with double data entry and range checks. Access to the trial dataset is restricted to investigators.

The primary outcome of the study is defined as responders who have a decrease in the weekly average of worst abdominal pain scores of ≥30% compared with baseline and a weekly increase of ≥1 CSBM from baseline (24). To assess the response over time, data between 2 groups will be summarized and compared throughout the treatment period and at the end of follow-up.

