### Safety assessments

2.7

Data from patients who have had at least one acupuncture or sham-acupuncture session are included in the assessment of acupuncture safety. Safety profiles are assessed by documenting important AEs reported during each treatment session and in follow-up interviews. The severity and causal relationship of AEs to the interventions are assessed by the investigators. Additionally, physical examinations and clinical laboratory tests are conducted to monitor patient safety.

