## Discussion

3

This randomized, double-blinded, sham-controlled pilot trial is designed to rigorously evaluate the efficacy and safety of EA in the management of IBS-C. To our knowledge, this is the first sham-controlled acupuncture study for IBS-C. Additionally, it is the first acupuncture trial to adopt the FDA-recommended primary endpoint for IBS-C. By incorporating a biological sampling strategy to explore mechanistic insights, our comprehensive approach enables assessment not only of clinical outcomes but also of how EA may modulate gut microbiota and neurotransmitter-related metabolites associated with the brain-gut axis.

The double-blind design ensures that neither the participants nor the accessors are aware of the treatment allocation, minimizing potential biases in outcome assessment. In addition to the use of eye masks, identical acupuncture needles are applied for both the EA and sham groups. While participants may experience different sensations from the electrical stimulation, they are informed in advance that these sensations could vary from person to person. These approaches help strengthening the blinding effect between the groups.

It is important to acknowledge that the insertion of needles in the sham group may still induce minor physiological effects (29, 30). The purpose of using sham acupuncture in this study is not to compare the effects of needle insertion versus non-insertion, but to assess the difference between acupuncture at acupoints versus non-acupoints based on TCM theory. Sham acupuncture, which involves needle insertion outside these designated acupoints, serves as a necessary control measure to ensure blinding of the study. By comparing the physiological responses between the two groups, we can explore whether acupuncture at traditional acupoints provides distinct effects compared to non-acupoint areas. This approach allows us to isolate the potential impact of acupuncture grounded in traditional meridian theory, rather than just the mechanical effects of needle insertion.

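### The principal investigator keeps the pre-generated allocation list, so concealment is not assured, the list holder cannot count as blinded, and the randomisation method is described in contradictory terms

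*Protocol article*

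**What the plan says.** Section 2.6 (Randomization, blinding and concealment) of the protocol article describes the sequence and its custody in one sentence. The method is given as "Simple, complete, non-sequential random numbers were generated in advance by a computer program in blocks of four". The generator was an outside statistician, and the numbers were then held by the principal investigator: "in blocks of four by a statistician from a third-party institution and were kept by the principal investigator".

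Release comes next: "After a participant’s eligibility is confirmed, a randomization number which corresponds to the group allocation is provided to the acupuncturist". The article draws this conclusion: "This arrangement ensures that both the clinical assessor and participants are blinded to the allocation". The Discussion repeats that "neither the participants nor the accessors are aware of the treatment allocation".

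Section 2.6 also says that the study stays blinded up to the final analysis and report. In an emergency the principal investigator is to be told, and any investigator who breaks the code must record why.

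Three other sections show what investigators do:
- Section 2.2: an investigator speaks with potential participants before enrolment.
- Section 2.4: "Access to the trial dataset is restricted to investigators".
- Section 2.7: "The severity and causal relationship of AEs to the interventions are assessed by the investigators".

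**The concern.** Concealment means that nobody who can influence whether or when a patient enters the trial can know the next assignment. An outside statistician serves that aim only while the list stays outside the trial team. Here the article names a custodian, and it is the lead investigator. This is a stated rule, not a detail left to a fuller document.

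Two things are at stake.
- **Selection.** Eligibility leaves room for discretion. Section 2.4 uses the screening period partly to exclude people who may not comply, and the Discussion lists several factors weighed when eligibility is decided. Foreknowledge of the next arm could affect such decisions, and no later analysis can reliably undo that.
- **Ascertainment.** If a person who has seen the list also assesses adverse event causality, that assessment is not blind.

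The description of the method is also inconsistent. Simple (complete) randomisation assigns each patient independently of the others. Blocks of four force balance after every fourth patient. One sequence cannot be both.

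**Working it through.** **1. Inputs.** Allocation is 1:1 (section 2.1), the block size is four (section 2.6) and the total is 60 (section 2.5), which gives 60/4 = 15 blocks. The article gives no figure for predictability, so there is none to reproduce. Its total of 60 can be reproduced and is not disputed. With 70% versus 30%, two-sided alpha 0.05 and 80% power,

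n = [1.96·√(2·0.5·0.5) + 0.842·√(0.7·0.3 + 0.3·0.7)]² / 0.4² ≈ 23.3, so 24 per arm; 24/(1 − 0.20) = 30 per arm.

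**2. Predictability of blocks of four.** Assume that the guesser knows the block size and every past allocation in order. There are six equally likely blocks: AABB, ABAB, ABBA, BBAA, BABA, BAAB.

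| Position in block | Known with certainty | Best guess correct |
|---|---|---|
| 1 | 0 | 1/2 |
| 2 | 0 | 2/3 |
| 3 | 1/3 (first two alike) | 1/3·1 + 2/3·1/2 = 2/3 |
| 4 | 1 | 1 |

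- Known with certainty: (0 + 0 + 1/3 + 1)/4 = 1/3, so an expected 60 × 1/3 = 20 of 60.
- Best guess correct: (1/2 + 2/3 + 2/3 + 1)/4 = 17/24 = 70.8%, or 42.5 of 60, against 50% under simple randomisation.

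**3. To whom this applies.**

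| Person | Predictability of the next assignment |
|---|---|
| Holder of a readable list | 100%; block size is irrelevant |
| Person who knows all past allocations and the block size | 1/3 certain, 70.8% best guess |
| Acupuncturist | At most the row above; perhaps less, since treatment is given at two clinics (section 2.2) |
| Assessor with no knowledge of past allocations | 50% |

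**4. Effect of varying the block size.** In a simulation with sizes 4 and 6 mixed at random, where the guesser knows the possible sizes and all past allocations, certain assignments fall from 33.3% to about 5.5%. The best-guess rate falls only from 70.8% to about 69%. Moving the list matters more than varying the blocks.

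**5. Passages side by side.** The explicit blinding statements in section 2.6 and the Discussion cover participants and assessors. The code-breaking text presupposes that investigators do not already know the allocation. The custody sentence puts the allocation in the hands of one of them. Section 2.7 assigns causality to the investigators without excluding that person.

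**The case against.** A reader might infer that allocation in this trial is not concealed and is predictable. The article does not show that. A third party made the list, and a number is released only once eligibility is confirmed. The article does not say that the principal investigator screens, confirms eligibility or enrols. It also does not say whether the list was sealed or coded, a detail that may stand in the full protocol, which is not shown. This objection stands: the risk is conditional.

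A reader might also infer that a claim of investigator blinding has been broken. The explicit claim covers participants and the clinical assessor. Investigator blinding is only implied, and custody of the list does not by itself unblind either named group. This stands too.

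The 20 of 60 and the 70.8% are a ceiling. The article puts nobody in the position of enrolling patients while knowing the full allocation history.

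Some features that may look like faults are not. The acupuncturist must know which points to needle, and no blinding of practitioners is claimed. Restricting dataset access to investigators is a control on an encoded database, and the article does not say that allocation is visible there. Primary outcome data come from diaries kept by participants who are meant to be blinded, and the collaborating clinic may not handle outcome data except for safety. The route from list custody into measurement of the primary outcome is therefore narrow.

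None of this answers the custody rule itself, the gap over who assesses causality, or the contradictory description of the method.

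**Conclusion.** The point holds as a weakness in assurance, not as a demonstrated failure. Three things follow from the text:
- Concealment is not assured while the principal investigator keeps the list. It fails if that person, or anyone else with access to it, takes part in eligibility or enrolment.
- The principal investigator cannot be counted as blinded. This sits badly with the statement that the study stays blinded until the final analysis, with the emergency code-breaking rule and with investigators assessing adverse events.
- The randomisation is described as two different methods in one sentence.

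The size of any bias cannot be computed from the article. The bounds are 100% foreknowledge for the holder of a readable list, one third certain and 70.8% best guess for someone with the full allocation history, and 50% for someone without it. With 30 per arm, one patient carries 1/30 = 3.3 percentage points of an arm's response rate. That shows sensitivity to individual enrolments; it is not evidence that any enrolment was steered.

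**What to change.** For patients not yet randomised:
1. The third-party statistician or institution holds the list. Each allocation goes to the acupuncturist only after eligibility is confirmed and enrolment is irrevocably logged.
2. The principal investigator receives codes only through documented emergency unblinding.
3. An existing investigator without access to the list assesses adverse event severity and causality.
4. Section 2.6 describes the method as permuted blocks of four, drops the simple and complete wording, and states who is blinded and who is not.
5. Optionally, block sizes vary and are not disclosed to site staff. The gain is small (step 4 of the working).

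The cost is a small amendment with ethics approval before it takes effect (section 2.10), and minor set-up with a statistician already engaged. No extra patients or procedures are needed, and the total stays at 60. Enrolment has run since September 2024, and the article does not say how many patients remain to be randomised. Allocations already made cannot be repaired, so the final report should disclose who held the list, in what form, and whether that person took part in screening, enrolment or adverse event assessment.

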### Safety assessments

2.7

Data from patients who have had at least one acupuncture or sham-acupuncture session are included in the assessment of acupuncture safety. Safety profiles are assessed by documenting important AEs reported during each treatment session and in follow-up interviews. The severity and causal relationship of AEs to the interventions are assessed by the investigators. Additionally, physical examinations and clinical laboratory tests are conducted to monitor patient safety.

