**Figure 1 fig1:**
[figure not shown]
Study flow.

**Table 1 tab1:** Schedule of study procedures.

Week	0	2	3	4	5	6	7	13
Visit	1	2–3	4–5	6–7	8–9	10–11	12–14	15
Eligibility assessment	✓	✓						
Informed consent	✓							
Baseline data collection	✓							
Concomitant drug record	✓	✓	✓	✓	✓	✓	✓	✓
Adverse effects assessment		✓	✓	✓	✓	✓	✓	✓
Physical examination and samples collection	✓	✓					✓	
Food frequency questionnaire (FFQ)	✓							
Short-form Wang Qi’s body constitution classification questionnaire (SF-CCMQ)	✓			✓			✓	✓
Questionnaires with psychiatric assessment	✓			✓			✓	✓
Intervention		✓	✓	✓	✓	✓	✓	

Patients are required to fill in their diaries daily from the start of the 2-week screening period until the end of the trial, recording the timing of bowel movements (BMs), stool consistency, degree of straining during defecation, sensation of complete or incomplete evacuation, and the name and dosage of any medications taken. Throughout the trial, patients are asked to avoid making significant lifestyle changes, such as initiating a new diet or modifying their exercise routine. Patients must discontinue any medications listed in the exclusion criteria before entering the trial. Concomitant medications that may affect IBS symptoms, such as antibiotics, antidepressants, probiotics, or herbal medicine, are prohibited for at least 1 month before the screening period. If a participant meets the inclusion criteria but needs to use medications due to a comorbid illness or changes in health status, it will be recorded in the case report form (CRF).

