Other measurements include: (1) Proportion of patients with an improvement of ≥30% in abdominal pain scores from baseline; (2) Proportion of patients with an average increase of 1 or more CSBMs per week as compared with the baseline; (3) Average number of SBMs, CSBMs per week; (4) Percentage of bowel movements with normal consistency; (5) Percentage of bowel movements with severe or very severe straining during defecation; (6) Median time to the first SBMs, CSBMs after first session of EA; (7) Average number of bisacodyl tablets or enemas used per week; (8) Global assessment of efficacy of treatment with Likert scale at mid-treatment, end of the treatment, and end of follow-up; (9) IBS-C related severity and quality of life scores such as IBS Symptom Severity Scale (IBS-SSS), IBS Quality of Life (IBS-QOL), Patient Assessment of Constipation Symptoms (PAC-SYM), Constipation Quality of Life (PAC-QOL) and Patient Health Questionnaire-15 (PHQ-15) at the start of the treatment, mid-treatment, end of the treatment, and end of follow-up; (10) Depression, anxiety, and stress symptoms in IBS-C patients by Hamilton Depression Scale (HAMD), Self-rating Depression Scale (SDS), Patient Health Questionnaire (PHQ-9), General Anxiety Disorder (GAD-7), Hospital Anxiety and Depression Scale (HADS), Visceral Sensitivity Index (VSI) and Perceived Stress Scale (PSS) at the start of treatment, end of treatment, and end of follow-up; (11) Patient expectancy and trust in treatment, assessed via a brief questionnaire at the start of treatment, end of treatment, and end of follow-up; (12) Feasibility outcomes, including recruitment and retention rates, adherence to treatment protocols, completeness and quality of symptom diaries and questionnaire responses, and documentation of adverse events throughout the study. In addition to the primary and secondary outcomes, dietary intake and TCM constitutional patterns are assessed using the Food Frequency Questionnaire (FFQ) and Short-Form Wang Qi’s Body Constitution Classification Questionnaire (SF-CCMQ).

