### Statistical analyses

2.9

All efficacy and safety analyses will be conducted based on intention-to-treat (ITT) principle. Missing values will be imputed by the last-observation-carried-forward method. Statistical analysis will be performed using the Stata software, with statistical significance defined as a two-sided *p*-value of <0.05. Baseline characteristics will be reported as mean (SD). Baseline differences between the groups will be evaluated using Student’s t-test for normally distributed continuous variables and the non-parametric Mann–Whitney U test for non-normally distributed variables. For categorical variables, the chi-squared test or Fisher’s exact test will be applied. Comparisons between groups will be conducted by using the unpaired t-test for normally distributed data and the Mann–Whitney test for non-normally distributed data. Within-group differences will be evaluated using the paired t-test for normally distributed data and the Wilcoxon signed-rank test for non-normally distributed data.

To minimize the risk of false positives, multiple-testing correction methods will be applied during the data analysis process where appropriate. Additionally, advanced statistical methods, including the Logistic Generalized Linear Mixed Model (GLMM), will be applied. Potential inter-center differences in study outcomes will also be assessed.

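### Safety section 2.7 captures AEs through an undefined filter narrower than the rest of the article, and sections 2.7 and 2.9 name different safety populations

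*Protocol article*

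**What the plan says.** **Capture of adverse events.** Section 2.7 gives the capture rule: "Safety profiles are assessed by documenting important AEs reported during each treatment session and in follow-up interviews". The article does not define which events count as important. The next sentence drops the qualifier: "The severity and causal relationship of AEs to the interventions are assessed by the investigators". Two other places carry no such limit. Table 1 has a row "Adverse effects assessment" ticked in every column from week 2 to week 13. The feasibility outcomes in section 2.4 include "documentation of adverse events throughout the study".

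**Safety population.** Section 2.7 states: "Data from patients who have had at least one acupuncture or sham-acupuncture session are included in the assessment of acupuncture safety". Section 2.9 states: "All efficacy and safety analyses will be conducted based on intention-to-treat (ITT) principle". The sentence that follows in section 2.9 is "Missing values will be imputed by the last-observation-carried-forward method", with no exception for safety data.

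**The concern.** The two problems are separate.

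First, the word *important* acts at the point of capture. If someone must judge an event important before it is documented, an event screened out is never graded for severity or causality, and no later analysis can recover it. The events most exposed are the minor ones that needling or current would be expected to produce. Under section 2.6 the acupuncturist is given the allocation, and under section 2.7 AEs are reported during treatment sessions, so a discretionary filter at that point could work differently in the two arms.

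Second, the article gives two denominators for the same safety analysis and attaches an imputation rule that does not suit event data.

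At stake are the safety results of a trial that names safety as an aim (Abstract and Discussion), lists AE documentation as a feasibility outcome, and is meant to inform larger trials.

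**Working it through.** **1. The denominator in the plan.** Section 2.5 gives response rates of 70% and 30%, two-sided alpha 0.05, power 80% and dropout 20%. With the pooled-variance formula and no continuity correction:

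n per arm = [1.960 × √(2 × 0.5 × 0.5) + 0.842 × √(0.7 × 0.3 + 0.3 × 0.7)]² / 0.4² = (1.386 + 0.545)² / 0.16 ≈ 23.3, rounded up to 24.

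24 / (1 − 0.20) = 30 per arm, 60 in total. This matches the stated size, so the ITT denominator is 30 per arm.

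**2. How far the two safety sets can differ.** Let k be the number of patients in an arm who are randomised but receive no session, and x the number with an AE. Section 2.9 gives x/30 and section 2.7 gives x/(30 − k). The gap is x·k / [30 × (30 − k)]. The article gives neither k nor x, so both are assumptions. With x = 6:

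| k | ITT (section 2.9) | At least one session (section 2.7) | Gap (percentage points) |
|---|---|---|---|
| 0 | 6/30 = 20.0% | 6/30 = 20.0% | 0 |
| 1 | 6/30 = 20.0% | 6/29 = 20.7% | 0.7 |
| 3 | 6/30 = 20.0% | 6/27 = 22.2% | 2.2 |
| 6 | 6/30 = 20.0% | 6/24 = 25.0% | 5.0 |

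The last row is an extreme: the whole 20% dropout allowance (0.20 × 30 = 6) lost before the first session.

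**3. LOCF applied to AE occurrence.** For a patient who withdraws without an event, carrying forward would assert that no event followed, although nobody looked. For a patient with an event at the last visit, it would repeat that event at later visits. A never-treated patient has no observation under treatment to carry. None of these outcomes is informative about harm.

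**4. The capture rule.** No calculation is possible here: the article gives no definition of importance, no expected AE rate and no recording share. What can be done is to set the texts side by side.

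- Section 2.7, capture sentence: important AEs, at sessions and in follow-up interviews.
- Section 2.7, next sentence: severity and causality for AEs, no qualifier.
- Section 2.4, feasibility outcomes: AEs throughout the study, no qualifier.
- Table 1: AE assessment in all columns from week 2 to week 13, no qualifier.

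The capture sentence is the narrowest of the four, and it is the one that tells staff what to document.

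**The case against.** **Full recording may be intended.** Section 2.7 does not say that *only* important AEs are documented. A reader might infer that AE rates will be incomplete. The documents do not support that certainty, because Table 1, section 2.4 and the next sentence of section 2.7 all point to wider recording. This stands: incompleteness is a risk created by inconsistent wording.

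**The definition may sit in the full protocol.** An article condenses, and AE definitions are commonly left to the fuller document. A missing definition alone would not be a finding. But the article states a capture rule that disagrees with its own schedule and outcome list, and that inconsistency is in the text shown.

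**Bias by unmasked staff is inferred.** A reader might conclude that the acupuncturist filters events and so biases the comparison between arms. No passage says who decides importance, and severity and causality go to the investigators. What the article does support is opportunity. The acupuncturist holds the allocation (section 2.6), and the collaborating clinic may handle data for safety purposes (section 2.2). Differential recording is conceivable but not shown, and any percentage put on it would be invented.

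**The two populations can be reconciled.** The ITT principle could mean analysis by assigned arm among treated patients, with the specific rule in section 2.7 taking precedence. That would remove the conflict, but the article does not say so.

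**LOCF need not mean AEs.** Section 2.9 speaks of missing values in general, and safety data also include laboratory tests and examinations, where a carried value at least has a meaning. This is fair. The defect is the lack of an exception for AEs, not a stated intention to impute them.

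**Conclusion.** The concern holds in a limited form. The capture sentence in section 2.7 uses an undefined filter that is narrower than Table 1 and section 2.4, so minor events may go unrecorded. Whether they would, and whether the loss would differ by arm, cannot be determined from the article.

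The safety populations in sections 2.7 and 2.9 conflict on their ordinary reading. The numerical effect is small unless several patients are randomised and never treated: nothing at k = 0, 0.7 points at k = 1 and 2.2 points at k = 3, assuming 6 AE patients in an arm of 30. The article suggests no value for k. LOCF has no sensible use for AE occurrence, and the text does not exclude it.

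A reader might also infer that safety must be analysed by treatment received. That is a convention the documents do not call for, and nothing in them suggests crossing between arms.

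The point is worth correcting because events lost at capture cannot be restored. It does not touch the primary outcome, the efficacy analysis or the sample size.

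**What to change.** In section 2.7, replace the capture sentence with one that records every AE at each treatment session and each follow-up contact, with severity, seriousness and relatedness. Make any selection by importance at the reporting stage only, by a stated criterion.

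In section 2.9, limit the ITT and LOCF sentences to efficacy. Add that safety is analysed in patients with at least one session, as in section 2.7, and that AEs are not imputed.

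The cost is a slightly longer AE log and a few changed sentences. No visit is added, since Table 1 already schedules AE assessment from week 2 to week 13. Enrolment began in September 2024, so the changes need IRB approval as an amendment (section 2.10). The report should say which participants were followed under the earlier capture wording.
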